### 3.4. Randomization and Blinding

In this study, the random numbers will be created by SAS (Version 9.3) (SAS Institute Inc., Cary, NC, USA). A nonparticipating statistician will manipulate the random numbers, who will inform the therapists of each randomized outcome via text message.

At the same time, depending on the particularity of acupuncture treatment, it is difficult to realize double-blind. In order to follow the principle of the blind method, the separation of the operator and statistician is strictly implemented throughout the whole research process. Firstly, when we start treating patients, all CRF participants do not know their grouping situation, and the operator selects corresponding treatment options according to a different grouping of subjects for treatment. Secondly, the data on gut microbiota in this study will be statistically analyzed by a third party, and the statistician will be unaware of the grouping and its clinical significance.

### 3.5. Sample Size

According to the results of previous literature (clinical study on an acupuncture fatigue group for cancer-related fatigue of qi and blood deficiency type), the average fatigue scale score of the control group was 5.17 ± 1.26, and the average score of the fatigue scale in the acupuncture group was 4.17 ± 1.14. In our study, we will set the following parameters: *α* = 0.05, 2-sided, power = 0.9. Our software PASS (Version 15.0) will be used to calculate the sample size of the treatment group and the control group, and the result is 30 in each group. Considering the loss of sample size caused by the 15% dropout rate, the final calculation will require at least 35 cases in the treatment group and 35 cases in the control group, and a total of at least 70 cases will be included.

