## 3. Design and Methods

### 3.1. Trial Design and Setting

This is a randomized controlled study to explore whether acupuncture can improve fatigue symptoms of CRF patients after breast cancer chemotherapy by regulating the gut-brain axis. Seventy participants will be randomly assigned to either the acupuncture group or the primary treatment group with 35 patients in each group in a 1 : 1 ratio. Relevant tests will be tested on both groups at the baseline and after 3 weeks of the treatment. Blood and feces will be collected at the beginning and end of treatment. Piper fatigue scale, KPS score scale, and quality-of-life scale will be used to observe the changes in fatigue symptoms and quality of life of CRF patients in two groups before and after treatment and to inspect the curative effect of acupuncture on CRF. Then, the method of ELISA will be used to explore the regulatory effect of acupuncture on the HPA axis and inflammatory cytokines. Moreover, based on 16SrDNA technology, the changes in gut microbiota structure and flora of CRF patients will be observed. Ultimately, the correlation analysis of gut microbiota content can be related to inflammatory cytokines, HPA axis, and clinical efficacy evaluation (Figure 1 and Table 1).

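### Section 3.5 is slightly off: its inputs need 31 to 32 evaluable patients per group, not 30, and 35 per group does not quite cover the stated 15% dropout

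*Protocol article*

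**What the plan says.** Section 3.5 takes its planning values from one earlier acupuncture study. For the comparator arm of that study it reports that "the average fatigue scale score of the control group was 5.17 ± 1.26". The value for the other arm is one point lower, with a slightly smaller SD: "the average score of the fatigue scale in the acupuncture group was 4.17 ± 1.14". The error rates are given as "0.05, 2-sided, power = 0.9". The software is named ("Our software PASS (Version 15.0) will be used to calculate the sample size") but the procedure within it is not, and the reported output is that "the result is 30 in each group".

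The dropout step follows: "Considering the loss of sample size caused by the 15% dropout rate", the plan asks for at least 35 per group, and "a total of at least 70 cases will be included". No inflation formula or rounding rule is printed. Section 3.1 fixes the same numbers for the trial itself ("35 patients in each group in a 1 : 1 ratio").

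Section 3.11 plans a two-sample t-test for between-group comparisons, with an unequal-variance t-test or a rank-sum test if the assumptions fail.

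**The concern.** Section 3.5 prints every input needed to recompute its result, and the recomputed number is not 30. The dropout allowance should then protect the evaluable number, but 15% off 35 leaves fewer than 30. Both discrepancies point the same way, towards less power than stated. This is also the only power statement in the article, although section 3.7 names three primary outcomes, so no other calculation supplies a margin. At stake is whether the stated 90% describes what 70 patients deliver for the outcome on which the trial was sized.

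**Working it through.** **Inputs** (section 3.5; 1:1 allocation from section 3.1)
- Difference: 5.17 − 4.17 = 1.00
- SDs 1.26 and 1.14; pooled SD = √((1.26² + 1.14²)/2) = √(2.8872/2) = 1.2015; standardised effect 1.00/1.2015 = 0.832
- Two-sided alpha 0.05, z = 1.960; power 0.90, z = 1.282

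**Step 1: the plan's 30 per group, normal formula**

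n = (1.960 + 1.282)² × (1.26² + 1.14²) / 1.00² = 10.507 × 2.8872 = 30.34, so 31 per group.

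The stated 30 is close, but even by this more lenient method it gives 89.7% power; 31 gives 90.6%. Other readings of the inputs do not return 30 either. By the same formula, a common SD of 1.14 gives 28, of 1.20 gives 31 and of 1.26 gives 34. With the pooled SD, one-sided alpha gives 25 and 80% power gives 23.

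**Step 2: the planned t-test**

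Power comes from the noncentral t distribution with 2n − 2 degrees of freedom and noncentrality 1.00/(1.2015 × √(2/n)):

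| Evaluable per group | t-test power |
|---|---|
| 29 | 87.6% |
| 29.75 | 88.4% |
| 30 | 88.7% |
| 31 | 89.7% |
| 32 | 90.6% |
| 35 | 93.0% |

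The smallest n that reaches 90% is 32. Unequal-variance degrees of freedom change none of these by more than 0.02 of a percentage point.

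**Step 3: the dropout step, taking 30 as given**

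- Needed to keep 30 after 15% loss: 30/(1 − 0.15) = 35.29, so 36
- Left from 35 after 15% loss: 35 × 0.85 = 29.75

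Two routes lead to the printed 35: 30 × 1.15 = 34.5 rounded up, or 35.29 rounded to the nearest integer. Either way fewer than 30 evaluable patients per group are expected.

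**Step 4: both steps together**

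- Strictly meeting 90% at 15% loss by the t-test: 32/0.85 = 37.6, so 38 per group, 76 in total
- By the normal formula: 31/0.85 = 36.5, so 37 per group, 74 in total
- With 70 randomised and 15% lost: 88.4% power at 29.75 per group, 87.6% if that is rounded down to 29
- With 70 randomised and none lost: 93.0%

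**Step 5: what baseline adjustment would recover**

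The residual SD is multiplied by √(1 − r²), where r is the correlation between baseline and follow-up Piper scores. The documents do not give r, so the range is shown, with one degree of freedom spent on the covariate:

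| Assumed r | Power at 29 per group | Power at 30 per group |
|---|---|---|
| 0.2 | 88.8% | 89.9% |
| 0.3 | 90.4% | 91.3% |
| 0.5 | 94.9% | 95.5% |

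**The case against.** The strongest reply is that the gap is too small to matter. At 29.75 evaluable per group, a true difference of 1.027 instead of 1.00, or a common SD of 1.17 instead of 1.20, already restores 90%. The planning values come from one earlier study and are far less certain than that. The text also says at least 35 per group, and the full 15% may not be lost over a three-week treatment period. All of this bears on the weight of the point and stands: the design is not undermined. It does not make 30 the right answer to the printed inputs, and section 3.1 fixes 35 per group in practice.

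Two stronger readings are tempting, and the documents do not support them:
- **That the dropout inflation was done the wrong way, by multiplying by 1.15.** No formula is printed, and 35 is equally consistent with the correct division rounded to the nearest integer. Only the shortfall is shown, not its cause. Likewise, that 30 is 30.34 rounded down is plausible but undocumented, because the PASS procedure is not named.
- **That 35 per group simply gives 88% power.** That holds only if the full 15% is lost. With 35 evaluable per group the power is 93.0%, so the stated 90% lies between the two cases.

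**Conclusion.** A minor point, but the section is wrong as written. For the stated inputs, 30 per group is one patient too few by the normal formula and two too few by the planned t-test. In addition, 35 per group does not preserve 30 after a 15% loss, whichever inflation or rounding was used. The loss of power against the stated 90% is 1.3 points at 30 evaluable per group, 1.6 at 29.75 and 2.4 at 29. Against a strict calculation the total is 4 to 6 patients short (74 or 76 versus 70).

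This rests on the printed means and SDs, equal allocation, the t-test as the analysis and, for the figures at 29 and 29.75, the full 15% loss falling equally on both groups. It concerns the fatigue score only.

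**What to change.** Keep 70 patients and restate section 3.5 along these lines: *35 per group; if 15% drop out, about 29 to 30 evaluable per group give about 88% power (93% with no dropout) for a difference of 1.0 with SDs of 1.26 and 1.14, two-sided alpha 0.05.* Name the PASS procedure used, and state that the dropout inflation is n/(1 − 0.15), rounded up.

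Optionally, make the primary fatigue comparison an ANCOVA adjusted for the baseline Piper score, which sections 3.7 and Table 1 already collect. Assuming a baseline-to-follow-up correlation of at least 0.3, which the documents do not give, power is then at least 90% to 91% at 29 to 30 evaluable per group; at 0.2 it stays just under 90%. This would change the analysis in section 3.11, so it should be fixed before any outcome data are examined by group.

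The cost is a wording change and a slightly less favourable power statement. No extra patients or measurements are needed.

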### 3.6. Intervention

The different treatments will be performed for thirty-five participants in each group. They will have experienced it five times a week for three weeks in separate compartments. These therapists are experienced doctors who have obtained medical qualifications. Before the trial, they will receive training to ensure adherence to the study protocol. Meanwhile, each therapist will be kept ignorant of the group allocation. The various separate interventions in two groups are as follows.

In the treatment group, according to the relevant literature research, the most commonly used acupoints for the treatment of CRF were summarized, and Zusanli (ST36), Sanyinjiao (SP6), Qihai (CV6), Guanyuan (CV4), and Baihui (GV20) will be selected. The orientation of acupoints derives from the planning textbook of traditional Chinese medicine colleges and universities, *Acupuncture and Moxibustion Science*. First, in the study, the therapists will use the single-use sterile needles (Hwato, Suzhou, China) to puncture these patients. 40 mm long needles (0.35 mm in diameter) are used to puncture points on the limb and abdomen. 25 mm long needles (0.3 mm in diameter) are used for head points. All needles are manually manipulated by flat reinforcing and flat reducing methods to create the certain experience termed as De Qi that occurs in both the patients and therapists. Participants will receive five acupuncture sessions per week, and each session will last for 30 min. In the control group, participants will take on aerobic exercise through jogging mode, in which the heart rate will be controlled at 50% of the maximum heart rate (maximum heart rate = 220 − patient′s age). They will also receive five exercise sessions per week, and each session will last for 30 min.

### 3.7. Primary Outcomes

We have three primary outcomes for this study: assessing the improvement of fatigue, physical performance, and the quality of life in CRF patients before treatment and 3 weeks after treatment. All evaluations will be performed by two professional physicians. They will be blinded to the treatment allocation.

The Piper fatigue scale will be used to evaluate the severity of fatigue before treatment and 3 weeks after treatment. It uses a 10-point scale of numerical descriptions, including nine items. Each item is rated on a scale of 0 to 10, with 0 indicating no fatigue and 10 indicating the most severe fatigue. In addition, 1 to 3 is for mild fatigue, 4 to 6 for moderate fatigue, and 7 to 10 for severe fatigue, and the fatigue integral is the total divided by 9. Overall, the higher the scores get, the more tired patients feel.

The KPS rating scale will be used to evaluate the body function status of patients before and 3 weeks after treatment. The KPS score is the functional status rating criterion. And the higher the KPS score gets, the better the health and physical status will be. Besides, it is generally believed that the KPS score above 80 is independent, 50-70 is divided into the semi-independent level, and below 50 is a dependent score, meaning someone needs help in their life. Patients with scores greater than 80 will have better postoperative status and longer survival time.

The EORTC core quality-of-life scale will be used to evaluate patients' quality of life before treatment and 3 weeks after treatment. QLQ-C30 (V3.0) is the most widely used method in the world to measure the quality of life of cancer patients. The inventory consists of 30 questions, from five kinds of function (physiology, daily life, cognitive, emotional, and social functions), three kinds of symptoms (fatigue, pain, nausea, and vomiting) and overall health status, the overall quality of life, and another separate six (sleep, appetite, diarrhea, constipation, difficulty breathing, and economic status) to measure the patient's quality of life. All the measurements were combined to get a score, which was proportional to the quality of life of the patients.

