### 3.11. Statistical Analysis

Data analysis will be conducted by using the IBM SPSS for Windows (Version 21.0). Basic descriptive statistics (mean and SD ($\overset{¯}{x}\pm s$)) will be reported for the characteristics and outcomes of each participant. The statistical significance is defined as *P* < 0.05 for all statistical analyses.

The Piper fatigue scale, KPS score, quality-of-life score, expression levels of HPA axis-related factors and inflammatory cytokines, and DNA copy number of gut microbiota are all measurement data. When comparing between groups, if the normal test and homogeneity test of variance are met, the *t*-test of two independent samples will be used. If it meets the normal test but does not meet the homogeneity test of variance, two independent sample-corrected *t-*tests will be used. If the normal test is not met, the Wilcoxon Man-Whitney *U* rank sum test for comparison between the two samples will be used.

The correlation analysis between gut microbiota and clinical efficacy score, HPA axis-related factors, and inflammatory cytokines will be performed using Pearson correlation analysis (for data obeying normal distribution) or Spearman correlation analysis (for data not obeying normal distribution).

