Therefore, we will choose Zusanli (ST36), Sanyinjiao (SP6), Guanyuan (CV4), Qihai (CV6), and Baihui (GV20) acupuncture points to perform acupuncture treatment on CRF patients after breast cancer chemotherapy. In our study, we will confirm that acupuncture therapy can reduce fatigue, improve the physical status, and improve the quality of life in CRF patients after chemotherapy for breast cancer. Moreover, acupuncture treatment will lead to changes in the HPA axis, and the expression level of ACTH in the serum is lower than that in the control group, while the expression level of CORT is higher than that in the control group. In addition, acupuncture treatment will reduce the expression levels of inflammatory cytokines IL-1*β*, IL-6, and TNF-*α* in the serum and further identify its effect on inflammatory cytokines and immune regulation. Finally, the changes in gut microbiota structure and genus in the acupuncture group and the control group will be observed, and further correlation analysis will be conducted with the HPA axis, inflammatory cytokines, and clinical efficacy evaluation. In all, acupuncture therapy will regulate the changes of CORT and ACTH hormone levels in the HPA axis by affecting the changes of gut microbiota and inhibiting the activation of inflammatory cytokines, and ultimately reduce the level of cancer-related fatigue in breast cancer patients.

If the primary hypothesis of this study is proven, acupuncture treatment has the potential to be used for reducing fatigue sensation and improving the quality of life of patients with breast cancer. Acupuncture therapy of traditional Chinese medicine would offer an alternative treatment modality and objective evidence for the treatment of CRF after chemotherapy for breast cancer and then alleviate the economic burden on patients and the society. Ultimately, the proposed study will also provide the clinical and theoretical bases for its extensive application of acupuncture therapy in tumor rehabilitation.

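### Three unranked primary outcomes are each tested at P < 0.05 with no success rule: familywise error is up to 14.3% if any one suffices, and if all three are needed the 0.9 power covers fatigue only

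*Protocol article*

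**What the plan says.** Section 3.7 of the protocol article lists the primary outcomes: "We have three primary outcomes for this study: assessing the improvement of fatigue, physical performance, and the quality of life in CRF patients". They are measured by the Piper fatigue scale, KPS and EORTC QLQ-C30, and none is placed above the others.

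Section 3.11 gives each outcome its own two-group comparison (t-test, corrected t-test or rank-sum test) and one threshold: "The statistical significance is defined as *P* < 0.05 for all statistical analyses". It states no testing order, adjustment or success rule.

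Section 3.5 rests the sample size on one outcome, taken from an earlier study: "the average fatigue scale score of the control group was 5.17 ± 1.26". The matching figures for acupuncture are a mean of 4.17 and an SD of 1.14. Alpha is set at "0.05, 2-sided, power = 0.9". The result is 30 per group, raised to 35 for 15% dropout. KPS and QLQ-C30 do not enter the calculation.

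Section 4 points two ways. One sentence expects to confirm benefit on fatigue, physical status and quality of life together. A later one begins "If the primary hypothesis of this study is proven", without defining that hypothesis, and goes on to mention fatigue and quality of life but not physical status.

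**The concern.** With three equal primary outcomes, the reader must know whether one significant result is enough or all three are needed. The two rules have different error rates and different power, and the article commits to neither.

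Under an any-one rule, the chance of a false positive exceeds the 0.05 used in the sample size. Under an all-three rule, the power of 0.9 describes one of the three tests and not the trial. While the rule is unstated, it can be chosen after the results are known. This governs the trial's main conclusion.

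**Working it through.** **Inputs from the documents.** Three primary outcomes (3.7); P < 0.05 for each (3.11); fatigue means 5.17 and 4.17, SDs 1.26 and 1.14, two-sided alpha 0.05, power 0.9, 30 evaluable per group, 15% dropout (3.5).

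**Assumed.** The correlation between the three test statistics is not given. It is taken as equal for each pair and varied from 0 to 0.9. Results at non-zero correlation come from simulating three correlated normal test statistics.

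**1. The plan's own figure (fatigue only).**
- Pooled SD = √[(1.26² + 1.14²)/2] = √1.4436 = 1.2015; difference = 1.00.
- n per group = 2 × (1.960 + 1.282)² × 1.4436 / 1.00² ≈ 30.3, so 31 (normal approximation); 32 with the t distribution.
- Power at 30 per group is 0.897 (normal) or 0.887 (t).
- Dropout: 30 × 1.15 = 34.5, so 35.

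The stated 30 and 0.9 are therefore reproduced closely, for fatigue at the full alpha of 0.05.

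**2. Any one of three is enough.** With independent outcomes and no true effects, the chance of at least one two-sided P < 0.05 is 1 − 0.95³ = 0.143. With correlation:

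| Correlation | At least one P < 0.05, either direction | At least one favouring acupuncture |
|---|---|---|
| 0 | 14.3% | 7.3% |
| 0.3 | 13.6% | 6.8% |
| 0.5 | 12.5% | 6.3% |
| 0.7 | 11.0% | 5.5% |
| 0.9 | 8.4% | 4.2% |

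For a single outcome the two columns would read 5% and 2.5%.

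**3. All three are required.** A false claim needs every test to be significant, including at least one under a true null. Its probability cannot exceed that of the single test, so it is at most 5%. When all three nulls are true it is below 1% for correlations up to 0.7.

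Power is the weak side. No difference or SD is given for KPS or QLQ-C30, so it cannot be computed from the documents. As an illustration, suppose each outcome had the same power as fatigue:
- 0.885 each: joint power 0.69 at correlation 0 (0.885³ = 0.693), 0.79 at 0.7.
- 0.90 each: joint power 0.73 at correlation 0 (0.90³ = 0.729), 0.81 at 0.7.

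**4. Splitting alpha instead.** At 0.05/3 = 0.0167 per outcome with 30 per group, power for fatigue falls to 0.80 (normal) or 0.77 (t). Restoring 0.9 takes 40 or 41 evaluable per group. That is 40/0.85 = 47.1 or 41/0.85 = 48.2, so 48 or 49 enrolled per group against the 35 planned.

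**The case against.** A reader might infer that this trial's false-positive rate simply is 11-14%. The documents do not support that. The figure needs an any-one success rule, which is written nowhere, and a correlation of 0.7 or less, which is not given. QLQ-C30 itself covers fatigue and physical function, so it overlaps in content with the other two outcomes, and a higher correlation is possible. The figure also counts rejections in favour of exercise. For false claims of acupuncture benefit the inflation is smaller, though still more than double the nominal 2.5% at correlations up to 0.7. One sentence of section 4 is worded as a conjunction, under which type I error is not inflated at all.

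A reader might also infer from section 3.11 that error control is ruled out. That is too strong: all-three testing and fixed-order testing both use 0.05 for every test, and a testing order could sit in an analysis plan that is not shown.

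These points make the size of the problem conditional. They do not remove it. Section 4 does not settle the rule, since its own sentence on the primary hypothesis leaves out physical status. Naming three equal primary outcomes is a choice the article makes, not detail left for later. An analysis plan that split alpha would depart from the threshold in section 3.11 and leave section 3.5 too small.

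**Conclusion.** The point holds in conditional form. The protocol names three unranked primary outcomes, gives each the full 0.05, states no success rule, and sizes the trial on fatigue only.

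- If any one outcome suffices, two-sided familywise error is up to 14.3%, and false claims favouring acupuncture run up to 7.3% against a nominal 2.5%. Both shrink as the assumed correlation rises.
- If all three are required, type I error is at most 5%, but power for the trial's claim is not shown. The 0.69-0.81 range is illustrative, because it lends KPS and QLQ-C30 a power that nothing in the documents supports.

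The pair of alpha 0.05 and power 0.9 fits only a trial whose sole primary outcome is fatigue. That conclusion does not depend on the assumed correlations.

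**What to change.** Name the Piper fatigue score at the end-of-treatment assessment as the single primary outcome, tested at two-sided 0.05. It is the trial's stated question and the only outcome that was sized. Word that assessment time the same way in sections 3.1 and 3.7 and in Table 1.

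Make KPS and QLQ-C30 secondary. Either test them in a fixed order only if Piper is significant (for example QLQ-C30, then KPS), or report them with confidence intervals. Align sections 3.7 and 3.11 and both sentences in section 4, and define the primary hypothesis as the Piper comparison.

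The cost is protocol wording, plus a matching registry update if the entry (not seen here) lists three primary outcomes. The sample size stays at 70. The downside is that KPS or quality of life alone can no longer carry a positive claim.

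If the sponsor prefers to require all three outcomes, no alpha adjustment is needed. The protocol should then state that rule and say that the power of 0.9 applies to fatigue only.
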